### Assessments of eligibility

Children in the targeted age group who are currently referred to and/ or already in treatment for ADHD or under assessment for ADHD at one of the two Child Psychiatric Departments are invited to participate in the trial. The diagnostic assessment includes a clinical interview with the child and one or both of the parents using the Kiddie-Schedule for Affective Disorders and Schizophrenia (K-SADS) [39]. K-SADS is a widely used semi-structured clinical diagnostic interview for parents and children. Additionally, all children are assessed with Reynolds Intellectual Assessment Scales (RIAS) [40] and Behavior Rating Inventory of Executive Functions (BRIEF) (parent edition) [41]. Finally, children are included in the trial if they comply with the following inclusion and exclusion criteria:

### Inclusion criteria

The following criteria are required for inclusion: ADHD diagnosis according to K-SADS, age between 6 and 13 years (both inclusive), IQ above 80, and written informed consent. Additionally at least one standard deviation (SD) above the mean on the Plan/Organize subscale on the BRIEF verifying problems with organizational skills is required. Both children with and without pharmacological treatment are included in the trial, although we expect the majority of children to receive pharmacological treatment. Children are required to be on stable pharmacological treatment for at least 6 weeks before participation in the trial. Families are recommended not to change the child’s ADHD medication or initiate new medications during the trial period of 10 weeks; however, the final decision about medication is made by the parents and the treating specialist, who is unrelated to the trial. The study researcher team will inquire about possible changes in medication at assessment visits and all changes will be summarized and reported in the results paper.

### Exclusion criteria

Patients fulfilling any of the following criteria as assessed by the K-SADS are excluded: autism spectrum disorders, serious psychopathology requiring immediate clinical attention (e.g., severe depression or aggressive behavior), head injury or verified neurological disease, intelligence quotient (IQ) < 80, medical condition requiring primary treatment, or no informed consent from parents (Fig. 1).

**Fig. 1 Fig1:**
[figure not shown]
CONSORT flow diagram. Flowchart on participant enrollment and the randomization process

### Intervention

Children and their parents allocated to the intervention and control group will both receive treatment-as-usual (TAU) at the clinic, and this may include psychoeducation, counseling of parents and teachers at school, and for some children pharmacological treatment. TAU is very similar at both sites and will be recorded.

The intervention group will participate in manualized organizational skills training (OST) in groups ([name] & [name], in preparation). Parents and children from 4 to 5 families participate in ten weekly 1.5 h group sessions at the clinic. Each group is run by two therapists. In the first half of each session, children and parents are together, and in the second half, parents and children are in separate groups. The content of the intervention is adjusted with age-appropriate tasks: one set of tasks for younger children (6–9 years) and one for older children (10–13 years). The intervention targets organizational skills, planning, and time and task management (homework and school assignments).

### Comparator/control condition

Participants randomized to the control condition continue to receive TAU as scheduled during the trial. Participants randomized to TAU will be offered OST after the completion of end-point and 6-month follow-up assessments in order to promote retention. TAU is provided outside of the study and is not under control of the study investigators. TAU at the clinic is involving clinical assessment for ADHD and treatment. Assessment usually consists of a parent and child interview, questionnaires collected from both home and school and often a school observation. Additionally, the child undergoes cognitive and IQ tests. TAU for children with a clinical ADHD diagnosis is involving psychoeducation, counseling of parents and school, and possibly medical treatment. No concomitant treatments are specifically prohibited, but families are asked not to initiate new behavioral or pharmacological interventions for the duration of the intervention period of 10 weeks. Concomitant treatments are documented for each participant for the duration of the study and will be reported in the participants’ characteristic section of the results paper.

### Randomization

Every participant is assigned a participant number. Participants are randomized 1:1 to intervention or control treatment and stratified by trial site (“Aabenraa,” “Vejle”) and age (older/younger). The allocation sequence is computer-generated with a varying block size for which the investigators are blinded. Randomization is performed by a statistician unrelated to the trial. The research assistant (RA) who is carrying out allocation will have no access to allocation sequence. When the subject is ready to be randomized, the RA will send this subject’s ID (and information relevant to stratification) to the statistician. The statistician will enter the ID number in the web-based randomization algorithms and will inform the RA to which study condition the subject is allocated to. The RA will then inform the families about the allocation and enroll them in the trial.

### Blinding

As the current trial compares an intervention to TAU, it is not possible to blind the participants and their parents. Blinding will be employed in all other possible areas (e.g., administration of the cognitive tasks is carried out by blinded research assistants, randomization, and data analysis) (Fig. 2).

**Fig. 2 Fig2:**
[figure not shown]
Timeline of assessment phases in the trial. (1) BRIEF, Behavior Rating Inventory of Executive Functions. P, parent. T, teacher; (2) K-SADS, Kiddie-Schedule for Affective Disorders and Schizophrenia; (3) RIAS, Reynolds Intellectual Assessment Scales; (4) CANTAB, Cambridge Automated Neurocognitive Test Battery; (5) COSS, Children’s Organizational Skills Scales. P, parent. T, teacher; (6) ADHD-RS, Attention Deficit Hyperactivity Disorder-Rating Scale. P, parent. T, teacher; (7) WFIRS-P, Weiss scale of disability Parent Report; (8) OST, Organizational Skills Training TAU; and (9) treatment as usual

### General description of outcome measures

The following outcome measures are used in this trial:

*Children Organizational Skills Scale (COSS)*—a valid and reliable questionnaire [42]. COSS is a 4-point scale ranging from “hardly ever/never” to “just about all the time” and has 58 items for parents and 35 items for teachers. It has excellent internal consistency alphas for both parent and teacher items, αs = .98 and .97, respectively, and test/retest reliability *r* = .99 and .94, respectively.

*Behavior Rating Inventory of Executive Function (BRIEF)* [43] is an 86-item questionnaire for parents and teachers regarding different aspects of the child’s executive functions. It consists of eight clinical scales and two validity scales. BRIEF has shown high internal consistency (αs = .80–.98) and test/retest reliability (*r*s = .82 for parents, .88 for teachers).

*Cambridge Neuropsychological Test Automated Battery* (CANTAB) is a battery of digital cognitive tests. It consists of highly sensitive, precise, and objective measures of cognitive function [44]. In this trial, we are using the following tests: (a) a test of sustained attention (Rapid Visual Information Processing (RVP), (b) an executive functions measure (One touch Stockings of Cambridge (SOC), (c) a working memory measure (CANTAB Working Memory), (d) a measure of impulsivity (CANTAB Stop Signal Task (SST)), and (e) a measure of reaction time (CANTAB Reaction time task (RTI).

*ADHD-RS* is a 3 -point Likert scale for parents and teachers [45], and it consists of an inattention subscale (questions 1–9), a hyperactivity/impulsivity subscale (questions 10–19), and the Danish version of ADHD-RS also includes a conduct disorder subscale (questions 20–26).

*Weiss Functional Impairment Rating Scale (WFIRS)* is the only measure of functional impairment that looks at specific domains of functioning and has been validated in the ADHD population [46]. WFIRS is a 50-item Likert scale ranging from 0 (never or not at all) to 3 (very often or very much) and is targeting 6 different domains. WFIRS is psychometrically validated with an internal consistency >.8 for each domain and for the scale as a whole.

For an overview of all outcomes and assessments, please see Table 1.

**Table 1 Tab1:**
[figure not shown]
Outcomes and time points for assessment in the OST trial

^1^Kiddie-Schedule for Affective Disorders and Schizophrenia (K-SADS)

^2^Reynolds Intellectual Assessment Scales (RIAS)

^3^Behavior Rating Inventory of Executive Functions (BRIEF)

^4^Children Organizational Skills Scale (COSS)

^5^Attention Attention Deficit-Hyperactivity Deficit-Rating Scale (ADHD-RS)

^6^Cambridge Automated Neurocognitive Test Battery (CANTAB)

^7^Rapid Visual Information Processing (RVP); RS)

^8^Weiss scale of disability-Parent Report (WFIRS-P)

^9^Sockings of Cambridge (SOC)

^10^Stop Signal Task (SST)

^11^Spatial working memory (SWM)

^12^Reaction time task (RTI)

### Outcomes

#### Primary outcome

The primary outcome is the total score on the parent-rated behavior Children Organizational Skills Scale (COSS)-parent [42]. The COSS was translated into Danish following standard procedure for translation of questionnaires; it was first translated from English into Danish by an authorized translator and then back-translated into English by another authorized translator. The final translation was approved by the original developer and publisher.

#### Secondary outcomes

The following secondary outcomes will be assessed at baseline and the end of the intervention.
CANTAB Rapid Visual Information Processing (RVP)Children Organizational Skills Scale (COSS) (teacher edition) [42]Inattention subscale ADHD-Rating Scale (ADHD-RS-IV) (parent edition) [45].Behavior Rating Inventory of Executive Functions (BRIEF) organize subscale (parent edition) [41].Weiss scale of disability-Parent Report (WFIRS-P) [46]

#### Exploratory outcomes

The following exploratory outcomes will be assessed at baseline and at the end of the intervention:
BRIEF (parent and teacher-edition)Inattention subscale assessed by ADHD-RS-IV (teacher edition)ADHD-RS-IV (parent and teacher): hyperactivity, ODD subscale and total scoreCANTAB one touch Stockings of Cambridge (SOC)CANTAB Working Memory (WM)CANTAB Stop Signal Task (SST)CANTAB Reaction time task (RTI)

Additionally, all outcomes will be assessed again at the 6 month follow-up.

### Statistical plan and data analysis

#### Sample size

We are conducting a randomized controlled trial using the continuous response variable COSS-total parent rating from independent control and experimental participants allocated at a 1:1 ratio. The primary outcome measure COSS has been tested in previous trials [30, 31].

Using data from Pfiffner and colleagues [31], we conducted a sample size calculation based on the COSS total score by parent rating as primary outcome. Based on a minimal relevant difference of 0.30 and a standard deviation of 0.36, it requires 32 participants in each group to reach 90% power with 5% significance level. Furthermore, to have sufficient power to analyze secondary outcomes with standardized effect size 0.5 SD, the required sample size was doubled to *n* = 64 in each group, resulting in 80% power for the secondary outcomes using 5% significance level. Finally, to account for an expected dropout of 10% during the study period, the required sample size was increased to 71 in each group (total sample size *n* = 142).

#### Analytical model

Descriptive analyses will be conducted of patient characteristics and patient compliance issues (e.g., how many sessions each family has been attending). Since repeated measures of data will be collected for each participant, the primary and secondary outcomes will be analyzed as mean change from baseline to post-intervention using mixed linear regression models with random intercepts for patients, adjusted for the stratification variables (site and age) and the baseline value of the outcome variable. Medication status will be used as a covariate in data analysis. Furthermore, for the primary and secondary outcomes, mixed linear regression models will be used to perform subgroup analyses according to age. The participants will be divided into two age groups of children (6 to 9 years old and 10 to 13 years old). We will perform a test of interaction to assess whether the effect of the intervention is different among the younger children compared with the older children. If the *p* value of the test of interaction is < 0.05, we will present separate estimates for the two subgroups. Finally, exploratory per-protocol analyses of the primary and secondary outcomes will be conducted. In case of variance inhomogeneity or non-normality of the model residuals, cluster robust standard errors will be used. Multiple imputation methods will be applied in case of unbalanced missing data patterns in the control and experimental groups. All analyses will be conducted in Stata 16.

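### OST is delivered in groups, but the model has a patient intercept only: if outcomes correlate within therapy groups, standard errors are too small, and the stated 80% secondary power does not allow for it

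*Protocol article*

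**What the plan says.** All references are to the Protocol article.

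- **Intervention:** "Parents and children from 4 to 5 families participate in ten weekly 1.5 h group sessions at the clinic". The next sentence adds: "Each group is run by two therapists".
- **Comparator/control condition:** "Participants randomized to the control condition continue to receive TAU as scheduled during the trial". No study groups are formed in this arm.
- **Randomization:** "Participants are randomized 1:1 to intervention or control treatment", stratified by site and age band.
- **Sample size:** the calculation takes its data "from independent control and experimental participants allocated at a 1:1 ratio". The primary calculation is "Based on a minimal relevant difference of 0.30 and a standard deviation of 0.36", giving 32 per arm for 90% power. The number is then doubled to 64 per arm for an effect of 0.5 SD, "resulting in 80% power for the secondary outcomes using 5% significance level", and raised to 71 for 10% dropout. No ICC or design effect appears.
- **Analytical model:** primary and secondary outcomes are analysed with "mixed linear regression models with random intercepts for patients", adjusted for site, age and the baseline value, with medication status as a covariate. Cluster-robust standard errors are a fallback if residuals are non-normal or their variance is unequal. The clustering unit is not named.

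**The concern.** Children in one OST group share two therapists, ten sessions and each other, so their post-intervention scores may be correlated. TAU children have no such grouping. The design is therefore partially nested, with clustering in one arm only.

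Nothing in the stated model captures this:

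- A patient intercept describes correlation between one child's own repeated scores, not between children in the same group.
- Site and age band form four cells, against about 14 to 18 OST groups (71/5 = 14.2; 71/4 = 17.75), so most between-group variation would remain.
- The robust-error clause is triggered by residual diagnostics. Within-group correlation can be present when residuals are normal with equal variance. The only grouping level in the model is the patient.

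At stake are the confidence intervals and p-values of the primary and secondary outcomes. The age-by-treatment interaction test is affected too, and its 5% threshold decides whether subgroup estimates are presented.

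**Working it through.** **Reproducing the plan's figures.** Two independent means, two-sided 5% (sidedness is not stated, but two-sided reproduces).

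- Secondary: 0.5 SD with 64 per arm gives 80.1% by t-test and 80.7% by normal approximation. The stated 80% is confirmed, under full independence and with no baseline adjustment.
- Primary: 0.30/0.36 = 0.83 SD needs 31.3 per arm by t-test for 90% power, so 32 is confirmed.

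**Inputs for the check.** From the article: 64 evaluable children per arm; 4 to 5 families per group, so m = 4.5; effects of 0.5 SD and 0.83 SD. Assumed, because the article gives none: ICC of 0.01, 0.05, 0.10 and 0.20.

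**Formulas.**

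- Design effect, OST arm only: DE = 1 + (m − 1) × ICC. The TAU arm has DE = 1.
- Variance inflation of the difference between arms: f = (DE + 1)/2.
- True SE divided by model SE: √f.
- Actual two-sided type I error: 2 × [1 − Φ(1.96/√f)].
- Power of a valid 5% test: noncentral t on 126 df, with noncentrality d × √(64/2)/√f.

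Worked line for ICC 0.10: DE = 1 + 3.5 × 0.10 = 1.35; f = 2.35/2 = 1.175; √f = 1.084; type I error = 2 × [1 − Φ(1.96/1.084)] = 7.1%; noncentrality at 0.5 SD = 0.5 × 5.657/1.084 = 2.61, so power is about 74%.

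| ICC (assumed) | DE, OST arm | True SE above model SE | Type I error | Power at 0.5 SD, unadjusted | Primary power |
|---|---|---|---|---|---|
| 0.01 | 1.035 | 0.9% | 5.2% | 79.5% | >99% |
| 0.05 | 1.175 | 4.3% | 6.0% | 76.8% | >99% |
| 0.10 | 1.35 | 8.4% | 7.1% | 73.5% | 99% |
| 0.20 | 1.70 | 16.2% | 9.2% | 67.6% | 98% |

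**Simulation check.** An unclustered t-test, 40,000 trials per setting, groups of 4 and of 5, zero mean effect with groups that differ: type I error was 6.0% and 5.9% at ICC 0.05, 6.8% and 7.1% at 0.10, and 8.6% and 9.5% at 0.20.

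**Effect of baseline adjustment.** The planned model adjusts for baseline and the 80% takes no credit for it. Multiplying the variance by (1 − r²), with r an assumed correlation between baseline and post-intervention score, and reading 0.5 SD as the unadjusted SD:

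| ICC | r = 0.4 | r = 0.5 |
|---|---|---|
| 0.05 | 84% | 87% |
| 0.10 | 81% | 85% |
| 0.20 | 75% | 80% |

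A small-sample df correction for 13 to 16 evaluable groups (64/5 to 64/4) takes off about 1 to 3 points in the unadjusted case.

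**The case against.** **The ICC is unknown and may be small.** This stands. At ICC 0.01 the SE changes by about 1% and type I error is 5.2%. A common ICC across parent ratings, teacher ratings and a computerised attention test is also unsupported. Manualised delivery and weekly supervision meetings may lower it. They do not justify fixing it at zero for every outcome.

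**Children are randomised individually, so a null treatment cannot inflate the error.** This stands in part. If OST and its groups change nothing for any child, grouping after randomisation does no harm beyond site and age composition, which the model adjusts for; a simulation of that case gave 5.0%. The 6 to 9% applies when groups truly differ but average zero. When the treatment works and groups differ, the understated SE still makes the intervals too narrow.

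**The trial is not shown to be underpowered.** This stands. A reader might infer from the unadjusted column that true secondary power is 68 to 77%. The article does not support that, because it plans to adjust for baseline.

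**Cluster size is slightly high.** If 10% drop out, evaluable group size is about 4.5 × 0.9 = 4.05. Design effects become 1.15 / 1.31 / 1.61 and type I error 5.9 / 6.8 / 8.6% at ICC 0.05 / 0.10 / 0.20, a small change.

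**A full protocol or analysis plan may add detail.** It may, but the article itself names the random effect and states independence, so this is a choice made rather than a detail left open.

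**Conclusion.** The point holds in conditional form. The analysis and the sample size both treat children as independent although OST is delivered in groups. For any positive within-group ICC the planned standard errors are too small. Over assumed ICCs of 0.01 to 0.20 the true SE is about 1 to 16% larger than reported, and type I error is about 5.2 to 9% when groups differ around a zero average effect. The discrepancy becomes material from an ICC of roughly 0.05.

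Two stronger readings are not supported. The documents do not establish that the error rate exceeds 5%, because they give no ICC. Nor do they show that the planned analysis falls below 80% power for secondary outcomes: at an assumed baseline correlation of 0.4 to 0.5, power with clustering is about 81 to 87% at ICC 0.05 to 0.10 and 75 to 80% at 0.20. What can be said of the 80% is that it assumes no within-group correlation and no baseline adjustment.

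Primary power is not in question, and no bias in the point estimate is claimed. Baseline adjustment may restore power, but it does not correct an SE that ignores the groups. The model is therefore the main fault and the power statement a lesser one.

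**What to change.** 1. Record the therapy-group ID for each OST child. Fidelity checklists are completed after every group session, so membership should be recoverable for children already treated.
2. In Analytical model, account for the group in the primary model for the primary and secondary outcomes: a random intercept for therapy group in the OST arm only, with TAU children as singletons. Add a small-sample degrees-of-freedom correction (Satterthwaite or Kenward-Roger), since only about 14 to 18 groups are expected.
3. In Sample size, state that the 80% assumes no within-group correlation and no baseline adjustment, and show it over a stated ICC range.
4. Do not enrol more participants on this account.

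The cost is one ID variable, one more variance term, a few sentences and slightly wider intervals. If the true ICC is near zero, little is lost. Recruitment was still under way when the article was written, so the change could be fixed before results are seen, when it is most credible.

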#### Monitoring of patient compliance issues

We are recording how many sessions each family has been attending. The OST group therapists are conducting treatment fidelity checklists after each session and register how well the parents and the children are participating in the sessions and if all of the aims for the session have been reached. Parents are asked to do some tasks with their child at home between sessions (e.g., making and implementing a reward chart). The homework is being reviewed in the following sessions and it is an item on the fidelity checklist. Additionally, at the end of the 10-week intervention, participating parents are asked to fill out a satisfaction survey regarding the intervention.

#### Data storage

All participant information is collected electronically at baseline and endpoints. Our questionnaires are located in the REDCap database, which is a secure web application compliant with the General Data Protection Regulation (GDPR) where questionnaire data is automatically stored. The REDcap has a log of data entry and verification. All data is collected using a participant number and is pseudo anonymized. Only study investigators and statisticians will have access to the final data set.

## Discussion

In this trial, we are investigating the effect of a non-pharmacological group intervention for children with ADHD targeting organizational skills in children. This trial is going to fill the gap in existing literature regarding how OST is working for younger children. Because organizational skills deficits are strongly associated with functional outcome, it is important to target interventions to improve these early in life. Although the target of OST is primarily organizational skills, many trials have found that the parents report improvements in their child’s attention. It is unclear if the parent reports indicate a real change or placebo effects, as parents mostly are not blinded to their child’s allocation. By investigating attention with an objective cognitive test, this trial is going to clarify whether OST can improve attention. Additional predictors of treatment response have so far only been investigated by one trial [47] and only in terms of symptom severity, parental anxiety, and IQ. We intend to use objective cognitive measures at baseline to investigate possible predictor effects.

In our meta-analysis of OST studies [34], we found that the most OST studies included children 8 years of age and older, with the exception of Mautone and colleagues [48], who successfully focused on children in kindergarten and first grade. Given that impairments in attention and organizational skill increase in severity with age, and due to the academic demands and decrease in adult supervision, clinical judgment suggests that earlier interventions may promote the acquisition of skills and avert future problems. Behavioral interventions for young children with ADHD are shown to reduce impulsivity and noncompliance [49], but deficits in attention and organization may be overlooked until older ages when compounded by functional impairments. Therefore, we extended the age to 6 years old, as many of the skills in OST are also relevant to younger children, who still need help from their parents. Children older than 13 years of age have different academic tasks and there are other OST interventions for teenagers [50].

Our trial design has several strengths: participants are all referred or in treatment in child and adolescent psychiatric services for ADHD, representing a real clinical sample of children with ADHD. All of our participants score at least one standard deviation above the mean at the plan/organize BRIEF subscale, thereby representing a sample of children with ADHD who have moderate to severe difficulties with organizational skills at baseline, preventing a ceiling effect of the intervention. Organizational skills training is an intervention that might be very feasible and useful in the clinics.

One limitation in our trial is that we are unable to conceal the group allocation from the families which might lead to a certain placebo effect. Additionally, our population group is limited to children with ADHD with possible comorbidities, but autism spectrum disorders (ASD) are excluded. Even though ASD is often comorbid with ADHD, children with ASD may have a wide range of additional treatment needs for the core and co-occurring symptoms other that inattention. OST is a focused treatment for organizational deficits in children with ADHD, and the main aim of our study is to test the efficacy of OST in children with ADHD. While many children with a primary diagnosis of ASD show some degree of ADHD symptoms, only 14% of children with a primary diagnosis of ADHD also have ASD, according to the CDC [51]. Our study is not powered to test moderating effects of co-occurring ASD, and this issue will likely require a separate, adequately powered clinical trial.

